### Randomisation and blinding

After the status survey, 200 housewives with similar ages and educational levels will be selected and divided randomly following a 1:1 ratio into an intervention group and a control group using SPSS. The study coordinator will be responsible for the randomisation and verification of the computer-generated treatment assignment with a randomisation table. All the investigators, except for the study coordinator, will be blinded. The participants will be instructed not to inform the other participants of their group assignment.

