### Health education intervention

Group A will receive health education through WeChat at 8.00 p.m. every 2 days. A previous study [37] has proven that WeChat push frequency has an impact on information dissemination. When the WeChat platform is used to provide education regarding edible oils, attention should be given to the time and frequency of intervention to avoid inciting negative behaviour among the participants. Thus, we will provide intervention every 2 days. Previous studies [38] have confirmed that the rate of reading articles published on WeChat accounts peaks at 9.00 p.m., and thus, we will publish the content at 8.00 p.m. to allow subjects to better accept the intervention and help us improve its effectiveness. Moreover, we will collect weekly feedback from the participants using two self-designed questions through WeChat: ‘Are you interested in the contents this week?’ and ‘What do you suggest for next issue’s content?’ The feedback will help us assess the satisfaction of the participants, and consequently, improve the contents and methods of intervention.

In accordance with the Chinese Dietary Guidelines [10] and the Chinese Dietary Reference Intakes, health education can be provided through lively presentations with text, images, videos and audios. The WeChat public platform will be used as the communication tool of the intervention group for 4 weeks. Content will include information regarding the negative effects of excessive edible-oil intake, facts about edible oils, suggested reasonable amounts of edible-oil intake and lectures on healthy oil use guidelines provided by nutrition experts. Information about the differences between saturated and unsaturated edible oils (Table 2) and their composition and nutritional properties will be provided to aid in edible-oil selection according to individual needs. Questions for increasing public interaction will also be included, such as ‘Did you control your oil intake today?’ and ‘Do you pay attention to your edible-oil intake?’ An interactive platform will be set up to allow nutrition experts to answer participants’ questions in real time. The process will last for 4 weeks, and the intervention effects on edible-oil usage will be evaluated immediately, 3 months and 6 months after intervention.

**Table 2 Tab2:** Fatty acid composition of common edible oils (%)

	Saturated fatty acid	Monounsaturated fatty acids (ω-9)	Polyunsaturated fatty acids		Trans fat

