### Quality control

To ensure the reliability of the survey data, the intervention programme will be established by the Department of Nutrition and Food Hygiene, School of Public Health and Management, Chongqing Medical University. The reliability and validity of the baseline and knowledge and attitude questionnaires will be tested.

A study manual will be provided before the survey, and training will be conducted among all the investigators. A standardised face-to-face questionnaire will be administered to the participants through the appropriate implementation and application of the unified method. Standardised experimental equipment and measurement methods will be used in the study, and kitchen scales will undergo quality control. To ensure that the weighing results of home cooking oil are accurate and reliable, the weighing range of the kitchen scales used in the survey will be set to 0–5 kg, with an accurate value of 1 g.

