## Discussion

In accordance with the experiment design, the intervention group will receive 4 weeks of intervention to determine whether differences in edible-oil knowledge and intake behaviour exist between the intervention group and the control group. The experimental design will ensure balance among the confounding variables in each group and will eliminate the bias caused by the characteristics of the participants. Given that the enrolled participants should be good at using the WeChat app, the samples will exhibit this bias from the beginning. To avoid potential biases during the entire process, we will strictly follow the inclusion criteria when recruiting participants and use blind methods to collect data during the implementation phase. In addition, to increase the participation rate and reduce the selection bias, we will use children’s health as an entry point. Given that the participants are women between the ages of 25 to 45 years, most of them will have children in their family. In China, children are considered ‘emperors’ in the family. Most women care about their children’s health; thus, we will provide knowledge about edible-oil consumption among children during the intervention.

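### The blinding statement is hard to reconcile with team-run WeChat delivery to one arm, and nothing protects it at the face-to-face outcome visits

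*Protocol article*

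**What the plan says.** Under Randomisation and blinding, the Protocol article states: "All the investigators, except for the study coordinator, will be blinded". The next sentence gives the only rule on disclosure: "The participants will be instructed not to inform the other participants of their group assignment".

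The Study procedure section gives group A education through WeChat every 2 days for 4 weeks and gives group B nothing. The Health education intervention section describes delivery in the first person plural: the team publishes the content in the evening, and "we will collect weekly feedback from the participants using two self-designed questions through WeChat". The answers are put to use: "The feedback will help us assess the satisfaction of the participants, and consequently, improve the contents and methods of intervention". In addition, "An interactive platform will be set up to allow nutrition experts to answer participants’ questions in real time".

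Outcomes are collected at three face-to-face visits (Knowledge, attitude and behaviour tests): immediately after the intervention and at 3 and 6 months. They comprise a 30-item knowledge and attitude questionnaire and a 3-day weighing of household oil. Quality control says of the survey: "A standardised face-to-face questionnaire will be administered to the participants". The Discussion lists, among the means of avoiding bias, that the team will "use blind methods to collect data during the implementation phase".

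**The concern.** The blinding statement covers every investigator but one, while the intervention needs people who deal with participants in one arm only. The difference between the arms is content against no content, so contact through the WeChat account reveals the arm. If anyone who does that work also counts as an investigator, the statement is not accurate.

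The second weakness lies at outcome collection. Participants cannot be blind to whether they received the education. They meet study staff in person three times, and the instruction they are given does not cover those staff. A participant could follow it fully and still tell the interviewer that she was in the WeChat group.

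The hypothesis is directional: more knowledge, more willingness and less oil in group A. An interviewer who knows the arm may prompt, explain or accept answers differently, or supervise the weighing differently. A trial report that repeated the statement would claim a safeguard that the described procedures do not secure.

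**Working it through.** No arithmetic applies. The check sets the sections side by side.

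1. **Who is said to be blinded.** Randomisation and blinding: all investigators, with the coordinator as the single exception. The section does not define the term investigator by role.

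2. **Who learns the allocation through delivery.** Study procedure: group A receives content and group B receives none. The control group gets the same information only after the 6-month follow-up, so this contrast lasts through all three outcome visits. Three tasks in Health education intervention therefore reveal membership of group A:
   - publishing content to participants every 2 days;
   - collecting and reading the weekly answers. The text speaks of participants in general, but one of the two questions asks about interest in that week's content, which only group A receives;
   - answering participants' questions in real time.

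3. **Who does these tasks.** The first two are described as done by the study team, and the third by nutrition experts. No section assigns them to the coordinator alone or to people outside the group of investigators. Statement 1 is consistent with step 2 only under such an assignment.

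4. **Who collects outcomes.** Quality control says that all investigators are trained before the survey and then describes the face-to-face questionnaire. On this usage the term appears to include the outcome collectors. No section keeps these people apart from those who run the account.

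5. **What keeps the outcome collectors blind.** Two things are needed: they must not learn the arm from the delivery work, and they must not learn it from the participant. The article states no separation of duties for the first. For the second, the instruction names other participants and no one else. The Discussion asserts blind collection but adds no mechanism.

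Blinded assessment is thus asserted in two places, and neither route by which it could fail is closed.

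**The case against.** The strongest reply turns on the word investigator. If it means the trained survey staff, as its use in Quality control suggests, then the blinding statement and the Discussion agree: survey staff are blind and the coordinator is not. The nutrition experts are named separately and never called investigators, and the first-person plural in the delivery section does not identify who runs the account. This reply stands as far as it goes. A reader might infer that the blinding statement is impossible to satisfy; the documents do not support that, because separate blinded assessors are compatible with the text. It does not close the gap at the visits, since even survey staff with no delivery role can be told the arm by a participant who has followed her instruction.

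A reader might also infer that group A has a weekly exchange with the experts. It does not: the weekly item is a two-question feedback form, and the expert answers are in real time with no stated schedule. The argument needs no weekly schedule.

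The outcomes also limit assessor discretion. Each questionnaire item has one correct answer worth one point, and oil is weighed on a calibrated scale with 1 g sensitivity. This narrows the scope for biased scoring. It leaves the conduct of the interview and of the household weighing open to influence.

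The protocol does not claim that participants are blind, and bias from their own knowledge of their arm would remain whatever is done about assessors. That is correct, and it limits what the fix can achieve.

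Finally, an article may leave duty rosters to a full protocol. The point here is different: the article makes a positive claim, relies on it, and fixes a disclosure rule that is too narrow for it.

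**Conclusion.** The concern holds in a limited form. The statement that all investigators but the coordinator are blinded is hard to reconcile with delivery and feedback run by the team in one arm only. Blinding of those who collect outcomes is possible but unprotected at all three visits.

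This rests on two readings: that the first-person plural in the delivery section includes people counted as investigators, and that the stated disclosure instruction is the whole of what participants are told. If a full protocol separates the roles, the first part becomes a matter of wording; the second remains unless the instruction is wider there.

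The size of any bias cannot be estimated. The document gives no basis for a figure, so none is offered. Unblinded assessment may move the results towards the hypothesis; the text does not show that it will.

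**What to change.** Make three changes:

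1. Restate Randomisation and blinding by role: participants, the coordinator and anyone who delivers WeChat content or handles feedback, including the experts who answer questions, are not blinded; outcome assessors are blinded. Align the sentence on blind data collection in the Discussion with this.
2. Extend the participant instruction so that women are asked not to reveal their group to visit staff as well as to other participants.
3. State that the three outcome visits are done by trained survey staff who do not handle the WeChat account.

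The cost is wording, one added line in the instruction, and some constraint on how existing duties are assigned. The article gives no staff numbers, so whether the split needs extra people cannot be judged from it. The abstract places the study in the design stage, so the changes can be made before recruitment.

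Two additions are optional: coded arms for the analyst, and a record of each assessor's guess of the arm at each visit, which would show afterwards how well blinding was kept.

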### Status survey

A self-designed survey questionnaire will be used to investigate the knowledge, attitude and behaviour related to edible oils of the 800 participants from Chongqing, China. Furthermore, the questionnaire can be used to screen participants who meet the inclusion criteria. The purpose of the questionnaire is to obtain the current status of and problems in edible-oil consumption among housewives in Chongqing. Questions related to edible-oil knowledge, attitude and behaviour are given 100 points. A high score corresponds to excellent knowledge and a positive attitude regarding edible-oil intake. Besides, in the questionnaire, we will ask who makes the decision on food choice in the household.

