### Sample size calculation and participants

Previous studies have indicated that the daily per-capita excessive edible-oil intake (the standard value is 25–30 g/day) in households is 79.6% [26]. We set *p* = 0.8, *q* = 1 − *p* = 1–0.8 = 0.2, margin of error *d* = 0.1, *p* = 0.08, *α* = 0.05 and *Z*_*α*2_= 1.96. The sampling size is *N*= $$ \frac{{Z_{\alpha /2}}^2\times pq}{d^2} $$ =1.96^2^ × 0.8 × 0.2/0.08^2^ = 96.04 families, and considering that the sample population in this item is female, then *N* ≈ 200. The participants’ non-response rate is 10%, and the questionnaire’s qualified rate is 90%; thus, the total required sample size is *N* ≈ 250. Finally, to obtain more comprehensive cross-sectional data, we expand the sample size by three times and recruit *N* = 3 × 250 ≈ 800 participants for the status survey.

During the intervention stage, we will select 200 participants to participate in a baseline survey from the status survey, which is based on their age and education to ensure that the demographic characteristics will have no significant difference. Subsequently, they will be divided randomly into an intervention group (group A) and a control group (group B) to conduct the intervention.

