### Participants and recruitment

Participants will be recruited from the following four areas (rural and urban) in Chongqing, China: Yuzhong District, Shapingba District, Dianjiang District and Wulong District. Each district represents a different level of economic development.

A publicity group will be set up during the early stage of the project. An advertisement with a short comic strip will be designed to present the study, and printed posters and leaflets will be disseminated in the cooperating communities. Women who are interested can register at the community centre. Community leaders can, if they find it appropriate, inform them about the possibility of participating in the study. Recruitment will also be done through announcements on microblogs and WeChat. Women who wish to participate will have to provide their informed consent and enrol on the study’s homepage if they meet the inclusion criteria.

The inclusion criteria are as follows: women who are between the ages of 25 and 45 years, involved mainly in housework (particularly cooking) and active daily users of WeChat (i.e. using WeChat more than three times daily).

The exclusion criteria are as follows: individuals who have never cooked, have been involved in other edible-oil experiments and those with cognitive or verbal impairments or diseases that require them to follow strict diets.

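### The status survey's margin of error assumes a random sample and its target is Chongqing housewives, but recruitment is by volunteering in four chosen districts

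*Protocol article*

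**What the plan says.** **Target.** The Status survey section gives the aim of the 800-woman questionnaire: "The purpose of the questionnaire is to obtain the current status of and problems in edible-oil consumption among housewives in Chongqing".

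**Size.** The section Sample size calculation and participants takes from a previous study that the "daily per-capita excessive edible-oil intake (the standard value is 25–30 g/day) in households is 79.6"%, rounds this to p = 0.8, and applies Z²pq/d² to reach 96.04 families. The margin is given as "margin of error *d* = 0.1, *p* = 0.08": it is labelled 0.1, while 0.08 enters the formula. The figure is then raised to about 200, to about 250 for non-response and unusable questionnaires, and to 800 because "to obtain more comprehensive cross-sectional data, we expand the sample size by three times".

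**Recruitment.** The section Participants and recruitment names four districts and an advertising campaign of posters and leaflets. "Women who are interested can register at the community centre", and "Community leaders can, if they find it appropriate, inform them about the possibility of participating in the study". Microblog and WeChat announcements are also used. Enrolment on the study homepage is for women who meet the inclusion criteria, one of which is using WeChat more than three times a day.

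**Bias.** The Discussion accepts that the sample is biased from the start by the need for WeChat skill. It then says: "To avoid potential biases during the entire process, we will strictly follow the inclusion criteria when recruiting participants". The same sentence adds blinded data collection, and the next offers children's health as a way to raise participation and reduce selection bias.

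**The concern.** A margin of error from Z²pq/d² describes chance variation when units are drawn at random from the population being described. Nothing in the article describes a sampling frame, a random draw or weights. Women enter because they saw an advertisement and were interested, because a community leader chose to tell them, or because they read an online notice. A woman's interest in oil and diet may well be related to what the survey measures.

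The article itself gives reasons to expect that who is sampled matters. The Background reports differences in oil intake between populations and regions. Participants and recruitment says that the four districts differ in economic development. Study procedure says that age and education are associated with intake behaviour, and the Discussion expects economic status to matter. A pooled result therefore depends on the mix of districts and recruitment routes.

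At stake is what phase 1 can conclude. Read as written, the plan lends the survey a precision and a population that the recruitment method does not deliver. Expanding the sample reduces chance error only.

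**Working it through.** **1. Reproduce the article's figure.** Inputs from Sample size calculation and participants: Z = 1.96, p = 0.8, q = 0.2.

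- With d = 0.08: 1.96² × 0.8 × 0.2 / 0.08² = 96.04. This matches.
- With the labelled d = 0.1: 1.96² × 0.8 × 0.2 / 0.1² = 61.5. This does not match, so 0.08 is the value in use.
- Doubling: 2 × 96.04 = 192.08, rounded to 200.
- 10% non-response and a 90% qualified rate: 200 / (0.9 × 0.9) = 246.9, rounded to 250.
- Expansion: 3 × 250 = 750, stated as about 800.

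The 800 is thus a multiple of an earlier figure and is not derived from a margin of its own.

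**2. The margin that random sampling would imply.** Half-width = 1.96 × √(0.8 × 0.2 / n):

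- n = 96: 8.0 points
- n = 250: 5.0 points
- n = 800: 1.96 × √(0.16/800) = 0.0277, or 2.8 points

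The 2.8 points is implied by n = 800 and is not stated in the article.

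**3. What a larger sample does when selection is biased.** The documents give no bias, so b below is an assumption shown over a range. The standard error is √(0.16/n), that is 0.0408 at n = 96 and 0.0141 at n = 800. The chance that a nominal 95% interval contains the true proportion is Φ(1.96 − b/SE) − Φ(−1.96 − b/SE).

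| Assumed bias b | n = 96 | n = 800 |
|---|---|---|
| 2 points | 92% | 71% |
| 5 points | 77% | 6% |
| 8 points | 50% | about 0% |

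For example, at b = 0.05 and n = 800: b/SE = 0.05/0.01414 = 3.54, and Φ(−1.58) − Φ(−5.50) = 0.058. The bias is the same in both columns; only the interval narrows around the wrong value.

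**4. How such a bias could arise.** Suppose the true proportion is 0.8 and women with excess intake volunteer at k times the rate of the others (k is an assumption). The survey then observes 0.8k / (0.8k + 0.2). For k = 0.5 this is 0.4/0.6 = 66.7%, and for k = 2 it is 1.6/1.8 = 88.9%. The error runs from −13.3 to +8.9 points. The two ends have opposite signs, and the documents do not say which applies, if either.

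**5. Set the sections side by side.** The sizing formula presumes a random draw, and the Status survey section names housewives in Chongqing. The recruitment section describes volunteers from four named districts. The first two cannot both hold with the third. The Discussion's remedies do not close the gap:

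- Applying the inclusion criteria strictly keeps ineligible women out but does not make the eligible volunteers representative. The WeChat criterion, where applied, is itself a source of the bias just conceded.
- Blinded data collection concerns measurement, not who takes part.
- Children's health as an entry point may raise participation, but the sample remains one of volunteers, drawn perhaps more from mothers concerned about health.

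**The case against.** The strongest reply is that the article makes few of the claims one might hold against it. Several stronger readings are tempting and are not supported:

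- **That the article prints a narrow margin for the 800.** It does not. The only margins in the text are 0.1 and 0.08, attached to 96.04 families; the 2.8 points is a calculation from n = 800.
- **That phase 1 will publish a prevalence of excess intake with a confidence interval.** No such output is stated. The Analysis strategy lists descriptive statistics and a regression, the status questionnaire is scored out of 100 points, and household weighing is described only for the tests after the intervention. The proportion of 0.8 serves for sizing, so the coverage figures illustrate the principle and do not predict a planned result.
- **That all 800 are frequent WeChat users.** The recruitment section ties enrolment to the criteria. But the Status survey section says that the questionnaire can screen for those criteria, and Study design says that it will collect information on WeChat use. The 800 may be a wider group.
- **That self-selection is ignored.** The Discussion concedes the WeChat bias and names a measure against selection bias. The measure is insufficient, but it is there.
- **That clustering by district widens the margin by a known amount.** The documents give neither an intracluster correlation nor the number of women per district. A cluster design effect is also doubtful for districts chosen on purpose, so none is claimed here.

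It is also fair to say that the study hypothesis concerns intervention against control and that the survey partly serves as a screening pool. This lowers the importance of the point. What remains is the mismatch between a random-sample formula, a Chongqing-wide target and volunteer recruitment, and none of these replies removes it.

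**Conclusion.** The point holds as a minor one. The sizing margin (labelled 0.1, used as 0.08) and the target population stated for the status survey do not follow from the recruitment described. Raising the number to 800 leaves any selection bias unchanged. This conclusion rests on the article's own text and needs no assumed figure.

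The size of the problem cannot be fixed from the documents. The bias of 2 to 8 points and the volunteering ratios of 0.5 to 2 are assumptions. They show that a bias of a few points would outweigh the implied 2.8-point margin, not that such a bias exists or in which direction it runs.

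A reader might infer that the trial result is compromised. It is not: the randomised comparison of groups A and B does not depend on the survey sample representing Chongqing, and its internal validity and power are not at issue here.

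**What to change.** 1. In the Status survey section, restate the target as volunteering women aged 25 to 45 in the four districts. Say whether the WeChat criterion is applied at survey entry and, if so, add daily WeChat use to the target.
2. In the sample size section, state that the margin assumes random sampling and is not a precision claim for Chongqing, and give one value of d.
3. Record recruitment route at enrolment (poster or community centre, community leader, WeChat or microblog). Describe survey results by district and route alongside any pooled figure.
4. In the Discussion, keep the admission of WeChat-related bias, but do not claim that following the inclusion criteria avoids it.

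The cost is some rewording, one extra recorded variable and a narrower claim for phase 1. Route should be recorded at enrolment, because it may not be recoverable reliably afterwards. Neither the sample size nor the randomised phase needs to change.
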